### 13. Data Safety and Monitoring

The Data Safety and Monitoring Board (DSMB) will oversee and provide advice to the PIs on the continued scientific integrity and safety of the implementation of the trial. At each meeting the board will review the status of recruitment, retention, successes, barriers and challenges of the implementation of the trial, adverse events and the reporting procedures of adverse events. Two interim analyses will be conducted in addition to the planned “final” analyses at the conclusion of the proposed study. These interim analyses will be conducted when 33.3% and 66.7% of the planned sample size have passed their 12-month follow-up assessment time point window. The DSMB will review findings from the interim analysis and determine whether the study needs to be terminated for safety reasons. Data will be sent to the DSMB a week prior to the meeting. The Board will meet twice a year. The meetings will be face-to-face. Minutes taken at the meeting will be archived. We have included a statement in the DSMP that the proposed Board members have no Conflict of Interest with the study. The DSMB will consist of four expert members in the field who are experienced with HIV treatment, substance abuse treatment, and vulnerable populations. The DSMB will meet twice a year. The DSMB will consist of three expert members in the field who are experienced with HIV treatment, substance abuse treatment, and vulnerable populations. Specifically the members will include:

1. [name], is the Senior Director of the Substance Abuse Treatment Evaluations and Interventions Research Program at RTI International. Since its inception in 1999, this program has evolved to include a multimillion dollar yearly portfolio. She is also

Adjunct Professor at the School of Public Health at UNC, Chapel Hill, and Adjunct Associate Professor of Psychiatry at Duke University School of Medicine. She has conducted multiple NIH-funded clinical trials testing gender specific HIV interventions with different populations of women drug users.

2. [name], is a Professor of Epidemiology and Public Health at Columbia University School of Public Health. He is an expert in addiction medicine and HIV care among drug users. [name] is an Associate Professor of Biostatistics at University of Pennsylvania. She is an expert in developing data analytic plans and analyzing outcome data for clinical trials and will perform the interim analyses.

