3. [name] is a Professor of Medicine at SUNY Downstate Medical Center. He has extensive experience conducting clinical research with HIV-infected women drug users.

**Interim Analyses and Stopping Rules:** Two interim analyses will be conducted in addition to the planned final analyses at the conclusion of the proposed study. These interim analyses will be conducted when 33.3% and 66.7% of the planned sample size (N=140 and N=280 women respectively) have passed their 12-month follow-up assessment time point window. Several considerations and/or constraints were balanced in deciding upon key aspects of interim analyses. We restricted the number of interim analyses to 2 in order to prevent too great a threat to valid statistical inference due to a theoretical need to adjust analyses to avoid Type I error inflation from multiple comparisons using the same data. Interim analyses will be conducted at the selected information rates (i.e., the 33.3% and 66.7% values) based on 12-month follow-up duration period as per recommendations in *Methodological Challenges in Biomedical HIV Prevention Trials* published in 2008 by the Institute of Medicine (IOM). Specifically, in the chapter entitled *Interim Monitoring and Analysis of Results*, the IOM recommended that stopping HIV prevention trials based on positive interim results should require evidence of a sustained impact. Thus, interim analyses will utilize complete data over the longest follow-up duration, i.e., the 12-month assessment time point. The Principal Investigators and Co-Investigators will be unblinded to the research, whereas the study staff will be blinded to the interim analysis. The interim analysis will be conducted by the statistician on the study and the results will be reported to the PIs. With respect to efficacy, stopping rules following an interim analysis focus on demonstrable benefit among the sample and data accrued to date.

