At each interim time point as well as after study completion, analyses will follow the data analysis plans for primary aims described in the original proposal. Interim analyses will focus on the study's primary aims. If at any of the interim analyses the statistical significance for all biological outcomes related to primary aims (i.e., cumulative STI incidence), exceeds the a priori  $\alpha < .05$  criterion at that time point, the study will be stopped since the inference will be that significant benefit of assignment to one study arm over the other will have already been demonstrated. We note that this represents two-sided hypothesis testing since demonstrating benefit with respect to disease prevention of one intervention over the other (regardless of the content of that intervention) is of public health value and importance. With respect to futility, stopping rules are concerned with effect size estimates indicating a null result is inevitable given the planned total sample size. Stopping a study in such circumstances avoids additional expenditure of time, fiscal, and human resources that would nevertheless ultimately result in lack of evidence of superiority of one intervention over the other. At each interim analysis time point, a post hoc power analyses will be conducted to determine the minimum sample size needed to achieve 80% power to reject the null hypothesis given point estimates and standard errors of efficacy estimates using data collected to date. If the estimated minimum sample size for power analyses using  $\alpha =$

.05 exceeds the planned enrollment of N=420 women for all of the biological and self-reported behavioral outcomes associated with the primary aims, the investigative team will notify the NIDA Program Official (PO) of such findings. Based on the magnitude of the difference between the estimated minimum sample sizes needed for 80% power and targeted sample size, in addition to recruitment rates to date, the investigative time and NIDA PO will discuss and agree whether the study should be stopped due to reasons of futility or whether modifications to the study design/protocols (e.g., increasing planned enrollment, hiring of additional recruitment staff, etc.) can be implemented to avoid futility.

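### Testing STI incidence at an unadjusted two-sided .05 at both interim looks and again at the end raises the type I error from 5% to about 10.7%

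*Supplement*

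**What the plan says.** The rule is in protocol section 13, under the paragraph on interim analyses and stopping rules.

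- **Looks.** "Two interim analyses will be conducted in addition to the planned final analyses at the conclusion of the proposed study". The interims fall at "33.3% and 66.7% of the planned sample size (N=140 and N=280 women respectively") past the 12-month window.
- **Trigger.** The efficacy stop depends on "all biological outcomes related to primary aims (i.e., cumulative STI incidence"), which is one composite outcome.
- **Level.** The study stops if the result "exceeds the a priori $\alpha < .05$ criterion at that time point".
- **Consequence.** Stopping is not advisory: "criterion at that time point, the study will be stopped since the inference will be that significant benefit".
- **Sidedness.** "We note that this represents two-sided hypothesis testing since demonstrating benefit".
- **Final analysis.** The same section applies the same primary-aim analysis plans at each interim and after completion.
- **Multiplicity.** The section describes the need to adjust as theoretical and answers it this way: "We restricted the number of interim analyses to 2 in order to prevent too great a threat to valid statistical inference".

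No group-sequential boundary, alpha-spending function or lower final level appears in section 13, in the power analyses (section 2.3) or in the Data Analyses Plan that follows section 18. The other copy of the protocol in the supplement carries the same rule.

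**The concern.** Each look at accumulating data gives chance another opportunity to cross the threshold. Restricting the looks to two bounds the inflation but does not remove it; what protects alpha is the level spent at each look. Here the full .05 is spent every time, and the first crossing ends the trial with a claim of benefit.

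Two things are at stake. The main STI claim would carry about twice its nominal error. And a stop at the first look would rest on very few infections, so the reported effect would be exaggerated and would carry into the cost-effectiveness aim. This also works against section 13's own rationale, which cites advice that early positive stopping should need evidence of a sustained impact.

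**Working it through.** **Inputs**

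- Looks at 140, 280 and 420 women, so t = 1/3, 2/3, 1 (section 13).
- Two-sided .05 at each interim (section 13).
- .05 at the final analysis. This is inferred: the same plans apply after completion, the futility calculation uses .05, and no other level is given.
- Event rates of 20.5% and, with a 50% reduction, 10.25%; 80% power; effective N 372, N 378 after ICC, 420 after 10% attrition (section 2.3).
- 1:1 allocation (Randomization section).

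**The plan's own sample size**

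A Wald formula for Poisson regression with a binary predictor, with null variance at the base rate, gives

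N = [1.960·√(4/0.205) + 0.842·√(2/0.205 + 2/0.1025)]² / (ln 2)² = (8.66 + 4.55)² / 0.480 ≈ 364,

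within 3% of 372. Then 378/0.90 = 420 exactly. The sample size is therefore reproduced, and it is that of a single test at two-sided .05 with no allowance for interim looks.

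**Type I error under the stated rule**

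Under the null, the three test statistics are jointly normal with corr(Zᵢ, Zⱼ) = √(tᵢ/tⱼ), that is 0.707, 0.577 and 0.816. The overall error is

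1 − P(|Z₁|, |Z₂|, |Z₃| all < 1.96).

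| After | Cumulative two-sided type I error |
|---|---|
| Look 1 (140) | 5.0% |
| Look 2 (280) | 8.3% |
| Final (420) | 10.7% |

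Simulated binary data with a pooled z test agree: 10.7% with 70/140/210 women per arm at a 20.5% rate, and 10.5% with 63/126/189 per arm (10% attrition) at a rate of 20.5% or 15%. Treating the looks as independent would give 1 − 0.95³ = 14.3%, which is too high because the looks share data. By symmetry, the false claim in favor of E-WORTH alone rises from 2.5% to about 5.4%.

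**What a first-look stop would show if the planned effect is true**

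Simulating 20.5% versus 10.25% with a pooled z test:

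| Women per arm at look 1 | Trials stopped | Typical infections when stopped | Median risk ratio when stopped (true 0.50) |
|---|---|---|---|
| 63 (10% attrition) | 35% | 20 | 0.31 |
| 70 (no attrition) | 39% | 22 | 0.33 |

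**Boundaries that hold 5% overall at t = 1/3, 2/3, 1**

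| Rule | Look 1 p | Look 2 p | Final p |
|---|---|---|---|
| O'Brien-Fleming (Z = 3.471, 2.454, 2.004) | .0005 | .0141 | .0451 |
| Haybittle-Peto | .001 | .001 | .0495 |
| Pocock | .0221 | .0221 | .0221 |

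With drift 1.960 + 0.842 = 2.80 (80% power for one test), O'Brien-Fleming power is 79.4%.

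**The case against.** The strongest objection is that the final level is never stated. Section 13 refers to plans in an original proposal that is not in the supplement, and tying the criterion to the time point could hint at look-specific levels. This is fair as far as it goes: the final .05 is an inference. But .05 is the only number given, no look-specific level is defined, and the two interims alone already use 8.3%.

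Other points, and what stands of them:

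- **Loss of recruitment is limited.** Section 2.1 starts enrollment in month 14 at 14 women a month. On steady accrual, woman 140 enters at month 24 and passes 12 months at about month 36. By then 22 × 14 = 308 women are enrolled, so a look-1 stop forgoes about 112. Woman 280 passes 12 months at about month 46, after enrollment ends, so a look-2 stop costs follow-up and not recruitment. This narrows the harm to the other aims; it does not touch the error rate.
- **The power cost depends on the comparator.** The rule as written has about 83.4% power at drift 2.80, so the drop to 79.4% is about 4 points. The extra power is bought with the inflated alpha; 80% is what the plan claims.
- **Futility stopping could offset some inflation.** That rule leaves the decision to discussion with the funder, so it cannot be relied on.
- **The board could intervene.** Section 13 gives the DSMB termination for safety reasons, while the efficacy stop is written as automatic.

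**Conclusion.** The rule is wrong as written and must be fixed. Applied as stated, it gives an overall two-sided type I error of about 10.7%, just over twice the nominal 5%. This assumes looks at one third, two thirds and full information and a final test at .05; without any final test the error is already 8.3%. The efficacy trigger is a single outcome, so no requirement for joint significance lowers these figures. The 35–39% chance of a first-look stop, and the median risk ratio of 0.31–0.33 in stopped trials, assume the planned effect is true and 63–70 women per arm are analyzed.

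**What to change.** In section 13 and the Data Analyses Plan, replace the .05 criterion with an O'Brien-Fleming boundary at information fractions 1/3, 2/3 and 1: nominal two-sided p of .0005, .014 and .045. A Haybittle-Peto rule (p<.001 at both interims, about .0495 at the end) is an acceptable alternative. State that the same boundary governs the final STI claim. If the looks move or the final sample size changes, the boundary must be recomputed, so naming the matching spending function is prudent.

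The cost is one paragraph and no added participants. Final power is 79.4% against the planned 80.0%. Early stopping for benefit becomes rarer: with the planned effect true, the chance of stopping at either interim falls from about 66% to about 43% under O'Brien-Fleming.

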## 2. Study Design and Statistical Procedures

2.1. Overview of Study Design: This RCT will be conducted with 420 drug-involved Black women recruited from probation, parole or designated ATI program sites in NYC. Women will be randomly assigned to either (1) the 5-session E-WORTH intervention condition that includes an individual Streamlined HIV Testing session or (2) a Streamlined HIV Testing session (See Section

C.9). Fortune providers will deliver both intervention conditions at the Fortune sites in Long Island City or Castle Garden in Manhattan. In extenuating circumstances (e.g. participants are located too far away from these sites), Fortune providers may also deliver both conditions at a NYC DOP sites approved by the appropriate DOP Assistant Commissioner or at our community research office. Women assigned to either condition will continue to receive all services provided by probation, parole or designated ATI program staff. Women who test positive for HIV in either condition will receive HIV post-test counseling and linkage to treatment using the CDC Counseling, Testing and Referral (CTR) Protocol. In month 14, recruitment of participants will begin. We will enroll an average of 14 women per month and complete enrollment by month 45. Self-reported data on behavioral outcomes will be collected from participants via audio computer-assisted self-interview (ACASI). The primary outcome will be measured via biological assay for infection by *Neisseria gonorrhea*, *Trichomonas*, and *Chlamydia trachomatis*, the most common STIs found among women in NYC.

Repeated measurements will take place at baseline and at 3, 6, and 12 months' post-intervention. For Aim 3, we will collect cost data from a variety of sources every six months from months 14-55. At midpoint during enrollment (Month 23), we will conduct a qualitative study on multi-level factors for Aim 4.

2.2 Statistical Procedures: The analytic approach is built upon the investigative team's prior HIV prevention RCTs, which involves an intention-to-treat approach, handling missing data using multiple imputation, and conducting sensitivity analyses to quantify robustness of findings based on models and their assumptions. Descriptive statistics will characterize the sample and measurement distributions to ensure proper application of multivariate methods. We will use multiple imputation to handle missing data. Attrition analyses will identify variables to be

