### 3.5. Randomization

Consistent with an intention-to-treat approach for data analyses, participants will only be considered enrolled in the trial when they have been randomly assigned to a study arm. We will implement urn randomization to “force” a balance (without adding bias) between study arms with respect to the number of women per arm so that half of the women will be randomized to E-WORTH and immediately receive the individual Streamlined HIV test session followed by 4 E-WORTH group sessions and half will be randomized to and immediately receive the Streamlined HIV Testing session alone. The randomization program, which has been adapted from our previous RCTs, will also feature a combination of randomization and assignments to balance the number of women per condition per site so that the number of women assigned to each condition will be distributed across probation, parole or designated ATI program and study sites. In addition, participants randomized to the intervention arm will complete the intervention individually if less than 4 participants are enrolled at a given site in 28 calendar days. Additionally, the assignment window during the Treatment as Usual condition assignment phase will open after the first participant is assigned. We will explain the randomization process to participants during informed consent. The randomization and assignment protocol will also

ensure moderators of intervention effects assigned to study arms, thus minimizing the possible introduction of bias that can occur with urn randomization or block permutation techniques.

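### The efficacy rule stops the study, not just enrollment, and has no rule for the roughly 55% (look 1) or 33% (look 2) of randomized women still short of their 12-month STI test

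*Supplement*

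**What the plan says.** Section 13, Interim Analyses and Stopping Rules, sets two looks, when "33.3% and 66.7% of the planned sample size (N=140 and N=280 women respectively) have passed their 12-month follow-up assessment time point window". The looks use 12-month data only. On a significant result for cumulative STI incidence, "the study will be stopped since the inference will be that significant benefit of assignment to one study arm over the other" is taken as shown. Nothing further is said about what stops: enrollment, delivery of the intervention, follow-up, or all three.

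Section 2.1 gives the accrual: "In month 14, recruitment of participants will begin", and "We will enroll an average of 14 women per month and complete enrollment by month 45". The total is 420.

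The Data Analyses Plan tests new incidence of any STI at the 12-month follow-up by logistic regression. The payment list in section 3.7 attaches an STI test to the 12-month visit; the 3- and 6-month payments are for an interview only.

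The supplement holds two copies of the protocol. The stopping rule and the accrual figures are the same in both.

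**The concern.** A 12-month endpoint with steady accrual means that many women are randomized but not yet assessed whenever a look is held. A stopping rule then needs two parts: what stops, and what happens to the women still in follow-up. The plan gives a broad answer to the first and none to the second.

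Taken literally, the rule would leave women already randomized without the STI result that the trial was set up to collect. The reported effect would rest only on the women counted at the look that triggered the stop. That estimate is exaggerated on average, because the stop occurs when the data happen to look favorable, and it is less precise than the data already in progress would allow.

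**Working it through.** **Inputs.** 420 women, 14 a month, starting in month 14 (section 2.1). Looks at 140 and 280 women past 12 months (section 13). Control risk 20.5%, halved to 10.25%, and 10% attrition (section 2.3). Two-sided .05 at each look (section 13).

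**The plan's own figures.** 420/3 = 140 and 2 × 420/3 = 280, which match. 378/0.90 = 420, which matches.

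**Who is in follow-up at each look.** The k-th woman is randomized k/14 months after the start and reaches 12 months at k/14 + 12. The number randomized by then is the smaller of 420 and 14 × (k/14 + 12).

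| | Look 1 (k = 140) | Look 2 (k = 280) |
|---|---|---|
| Months from first enrollment | 10 + 12 = 22 | 20 + 12 = 32 |
| Study month | 14 + 22 = 36 | 14 + 32 = 46 |
| Randomized | 14 × 22 = 308 | 420 (accrual takes 420/14 = 30 months) |
| Short of 12 months | 308 − 140 = 168 | 420 − 280 = 140 |
| Share of randomized | 168/308 = 54.5% | 140/420 = 33.3% |

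**Sensitivity.** If accrual is spread over 32 months (420/32 = 13.1 a month), look 1 has 297 randomized and 52.9% short of 12 months. The 12 months run from the intervention, so some delay is likely. With an assumed 3 months added at 14 a month, look 1 has 350 randomized and 60.0% short. Look 2 stays at 33.3% in every case tried.

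**Effect on the estimate.** Simulation of 400,000 trials: 20.5% against 10.25%, a two-proportion z-test at 1.96, and 90% of women evaluable. That gives 63 per arm at look 1 (140 × 0.9/2) and 126 at look 2. Completing follow-up of the 308 gives about 139 per arm (308 × 0.9/2); completing all 420 gives 189.

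- Trials stopping for E-WORTH benefit: 35% at look 1 and 30% at look 2, or 65% in all.
- Stopped at look 1: the mean risk difference is 16.9 points against a true 10.25. The women still in follow-up contribute unbiased data, so the completed estimate averages (63 × 16.9 + 76 × 10.25)/139 = 13.3 points (13.26 before rounding).
- Stopped at look 2: the mean is 11.7 points. Completed: (126 × 11.7 + 63 × 10.25)/189 = 11.2 points.

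**Precision.** The 95% half-width is 1.96 × √[(0.205 × 0.795 + 0.1025 × 0.8975)/n] = 1.96 × √(0.25497/n), with n per arm:

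| n per arm | 63 | 139 | 126 | 189 |
|---|---|---|---|---|
| Half-width (points) | 12.5 | 8.4 | 8.8 | 7.2 |

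So follow-up narrows the interval from 12.5 to 8.4 points at look 1 and from 8.8 to 7.2 at look 2.

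**Dependence on the boundary.** With O'Brien-Fleming bounds (3.471 and 2.454) the same simulation stops for benefit in about 2% of trials at look 1 and 41% at look 2, about 43% in all.

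**The case against.** The strongest reply is that stopping the study may mean stopping enrollment only. The text does not say that visits end, and it plans final analyses besides the interim ones. This stands in part: a reader might infer that these women cannot reach the endpoint, but the documents support only that they would not reach it if follow-up ends. The enrollment-only reading is weak at look 2, however, where enrollment is already complete and little but follow-up is left to stop. A data and safety monitoring plan and an original proposal are mentioned but not shown, so the gap can be stated only for the pages available.

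Four stronger readings are tempting and are not supported.

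- *Behavioral outcomes cut to 12-month completers.* The Data Analyses Plan fits mixed-effects models to these outcomes over the whole follow-up period, so women short of 12 months still contribute their 3- and 6-month data.
- *Early stopping as the likely path.* The 65% comes from the unadjusted boundary. With O'Brien-Fleming it is about 43%, nearly all at look 2.
- *A breach of intention to treat.* Section 3.5 says that "participants will only be considered enrolled in the trial when they have been randomly assigned to a study arm". That defines enrollment; an administrative stop does not by itself contradict it.
- *A conflict with the stated reason for the timing.* Section 13 says that "the IOM recommended that stopping HIV prevention trials based on positive interim results should require evidence of a sustained impact". Every woman counted at a look has passed her 12-month window, which meets that reason.

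**Conclusion.** The concern holds as a gap in the stopping rule. Followed literally, the rule gives up 12-month STI results already planned for about 168 of 308 randomized women (55%; 53–60%) at look 1 and 140 of 420 (33%) at look 2. A stop at look 1 would leave an estimate of 16.9 points where about 13.3 was available, with an interval about half again as wide. Continued follow-up reduces the exaggeration there but does not remove it. At look 2 the gain is mainly precision; the bias moves by only half a point.

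These sizes assume steady accrual at the planned rate, the planned effect, 10% loss, the plan's unadjusted .05 at each look, and a follow-up STI test at the 12-month visit only, as the payment list implies. A corrected boundary would change how often a stop occurs, but would not supply the missing rule.

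**What to change.** In section 13, replace the sentence that stops the study with: *Enrollment will be stopped. Every woman already randomized will complete her remaining planned assessments and her 12-month swab. The final intention-to-treat analysis will include all randomized women and will be reported next to the interim result that triggered the stop.* Add: *A positive second look does not end follow-up or the planned final analysis.*

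The cost is protocol wording, plus visits for about 140 to 168 women that are already in the planned trial and would run for up to about 12 to 14 months after a positive look. The final report would come later by about that time; the interim result can still be released when the look is held.

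### The futility criterion compares the N needed at the observed effect with 420, which does not show that a null result is inevitable, and the second look falls after planned enrollment closes

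*Supplement*

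**What the plan says.** Section 13 (Interim Analyses and Stopping Rules) places two interim analyses at 140 and 280 women past their 12-month assessment. It describes futility as concerned with "effect size estimates indicating a null result is inevitable given the planned total sample size". The operational rule is that "a post hoc power analyses will be conducted to determine the minimum sample size needed to achieve 80% power to reject the null hypothesis". The calculation takes as its effect the interim estimate with its standard error, at two-sided alpha .05. The trigger is met when the resulting sample size "exceeds the planned enrollment of N=420 women for all of the biological and self-reported behavioral outcomes associated with the primary aims". The team then notifies the NIDA Program Official. The two parties weigh how far the needed sample size exceeds the target, together with recruitment to date. They then decide whether to stop or to modify the study, for example by "increasing planned enrollment, hiring of additional recruitment staff, etc". No conditional or predictive power threshold is given.

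Section 2.1 starts recruitment in month 14 and states: "We will enroll an average of 14 women per month and complete enrollment by month 45". Section 2.3 gives the sizing: a 50% reduction from 20.5% cumulative STI incidence, 372 effective participants for 80% power, 378 after the ICC adjustment, and 420 after 10% attrition. Both copies of the protocol in the supplement carry the same futility rule.

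**The concern.** The stated aim and the calculation ask different questions. Whether a null result is inevitable depends on the data in hand and on what the remaining women could still contribute. The N for 80% power at the observed effect uses only the current point estimate, and asks whether it is smaller than the effect that 420 women would detect with 80% power. The trial was sized so that this effect is nearly the planned one. An estimate scattered around the planned effect will therefore fall short about half the time, even when the intervention does exactly what was hoped.

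At stake is a discussion about stopping or enlarging a trial that is on course. At the second look, the recruitment remedies also arrive after planned recruitment has ended.

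**Working it through.** **Inputs.** Section 2.3: 20.5% against 10.25%, 80% power, 372 to 378 to 420. Section 13: two-sided alpha .05, looks at 140 and 280, cut-off 420. Section 3.5 (Randomization): 1:1 allocation. Section 2.1: month 14 start, 14 women per month, follow-up counted after the intervention.

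**1. The plan's own figure.** A Poisson-regression formula with a binary covariate and null variance at the base rate gives (1.96×2 + 0.842×√(2 + 2/0.5))² / (0.205 × (ln 0.5)²) ≈ 364, within 3% of 372. A two-proportion calculation with 186 per arm gives 78.5% power. The attrition step is exact: 378/0.9 = 420. The sizing is therefore reproduced closely enough.

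**2. Where the cut-off lies.** With n women and observed statistic z, the N for 80% power at the observed effect is n(2.80/z)², where 2.80 = 1.96 + 0.84. This exceeds 420 when z < 2.80√(n/420).
- Look 1: 2.80 × √(1/3) = 1.62.
- Look 2: 2.80 × √(2/3) = 2.29.

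If 420 gives 80% power at the planned effect, the expected z at each look equals these values, so the STI component is met with probability 50%.

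**3. Dependence on the formula.** Summing exact binomial probabilities under 20.5% against 10.25%, with benefit stopping ignored:

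| Formula for needed N | Look 1 | Look 2 |
|---|---|---|
| Pooled two-proportion | 47% | 45% |
| Logistic Wald | 47% | 47% |
| Poisson log-Wald | 54% | 57% |
| Poisson, as in step 1 | 45% | 43% |

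**4. What crossing implies.** Conditional power at look fraction t under drift 2.80 is Φ[(z√t + 2.80(1−t) − 1.96)/√(1−t)]. At the look-1 cut-off this is Φ[(0.934 + 1.868 − 1.960)/0.816] = Φ(1.03) = 85%. In simulation under the planned effect, 67% of trials flagged at look 1 reach p<.05 if continued (66% with 90% retention and binomial data).

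**5. Second look with the benefit stop applied.** Section 13 stops the trial if STI reaches p<.05 at an interim look. With that rule in force, the STI component is met without a benefit stop in 34% of trials at look 2, and in 53-54% at one or both looks. Of those flagged at look 2, 51% would reach p<.05.

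**6. The full trigger.** Section 1.2 lists STIs, the number of unprotected acts and the proportion of unprotected acts. The documents give no behavioral effect sizes or correlations. Assume 80% power for each, so 50% per component. With three outcomes the joint chance per look is 0.5³ = 12.5% at correlation 0, and 1/8 + (3/4π)·arcsin(0.5) = 25% at correlation 0.5. If the behavioral outcomes have 90-95% power, it is about 3-19%.

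**7. Calendar.**
- The 140th woman enrolls at month 14 + 140/14 = 24, so look 1 is at month 36. By then 22 × 14 = 308 are enrolled and 112 remain.
- The 280th enrolls at month 14 + 280/14 = 34, so look 2 is at month 46 at the earliest, and later because follow-up runs from the end of the intervention.
- Enrollment ends at month 14 + 420/14 = 44, or 45 as stated. Spread evenly to month 45 (420/31 = 13.5 per month), look 2 moves to about month 46.7.

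**The case against.** The strongest reply is that the STI component is not the rule. Every primary-aim outcome must exceed 420, and Section 2.3 calls STI the rate-limiting outcome, so the lower joint figures may be nearer the truth. Crossing brings only notification and discussion, which must weigh the size of the shortfall. Near-misses should therefore be treated leniently. This stands, and it limits the severity. It does not rescue the criterion. Under the planned effect, the look-1 estimate calls for more than 840 women when z < 2.80√(140/840) = 1.14, which happens in about 32% of trials. The size of the shortfall is thus a poor guide as well.

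Four stronger readings are tempting, but the documents do not support them.

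- *The rule would fire half the time for an effective intervention.* That describes one component, and at look 2 it ignores the benefit stop.
- *A look-2 STI result with z between 1.96 and 2.29 triggers benefit and futility at once.* Only the STI component overlaps. Futility also needs every behavioral outcome to fail, and the benefit rule says that the study stops.
- *Enlarging on the unblinded effect inflates type I error.* This depends on an enlargement policy that the plan does not state. Simulated error is 4.6-5.0% if only trials needing at most 840 are enlarged. It is about 5.8-6.6% if all flagged trials are enlarged, up to two or three times 420.
- *Recruitment remedies are impossible at look 2.* They would mean reopening closed enrollment, which is difficult but not excluded. Cost data are collected to month 55.

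**Conclusion.** The point holds in limited form and should be corrected. The criterion does not measure what Section 13 says futility means. Under the planned effect its STI component is met about half the time at look 1 (43-57% across formulas at either look with benefit stopping ignored; about 34% at look 2 with it applied). Trials at the look-1 cut-off still have about 85% conditional power. These figures rest on the Section 2.3 planning values and, for conditional power, on a normal approximation with 80% power at 420.

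The chance that the full trigger is met is smaller, and it cannot be fixed from the documents: 12-25% per look under the stated assumption, and less if the behavioral outcomes are better powered. The consequence is a discussion, not a stop. The timing problem is confined to the second look, since about 112 women remain to be enrolled at the first.

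**What to change.** In Section 13, replace the needed-N criterion with conditional power for STI under the planned 50% reduction. Keep it non-binding and pre-state a low threshold. With 20% as an example, futility is considered at N=140 when z√(1/3) < 1.960 − 1.868 − 0.842 × 0.816 = −0.595, that is z < −1.03. Under the planned effect this flags P(Z < −1.03 − 1.62), about 0.4% of trials.

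Allow any enrollment increase only at the first look. Base it on the blinded pooled event rate, or use a final test adjusted for the unblinded change.

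The cost is Section 13 wording and a few lines of code. Futility will be flagged less often, including when there is no effect. At N=140 the 20% threshold flags P(Z < −1.03), about 15% of null trials, whereas the present STI component alone is met in P(|Z| < 1.62), about 89%. A higher threshold trades one error for the other, and the team should choose it openly. Dropping the N=280 efficacy look is not part of this change, because nothing here shows a fault in it.
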